## Abstract

**Background:**

It is well recognised that low back pain is a significant public health problem and engagement in moderate levels of physical activity is associated with positive outcomes.

Conservative active care, such as exercise, is effective in reducing pain and disability associated with chronic low back pain. However, a rapid decline in clinical outcomes is commonly seen after discharge from treatment.

**Methods/Design:**

We will conduct a randomised controlled trial to investigate the effectiveness of a mobile health supported physical activity intervention (compared to standard care) in care-seeking, pain and disability in people with chronic low back pain after discharge from treatment. We will recruit 68 patients with chronic low back pain following discharge from an outpatient hospital program, who will be randomly allocated to the physical activity intervention (*n* = 34) or the standard care group (*n* = 34) and monitored for 6 months. The physical activity intervention will involve a physical activity advice booklet, a face-to-face health coaching session and 12 fortnightly follow-up telephone-based health coaching sessions. This intervention will be supported by provision of a specifically designed web app and a physical activity monitoring device (*FitBit*). The standard care group will receive the physical activity advice booklet only.

**Discussion:**

This pilot trial will investigate a new model to prevent clinical decline in people following conservative treatment for chronic low back pain. If proven to be effective, this approach will constitute a major advance in the management of low back pain. Chronic patients who experience recurrent pain and disability after treatment are prone to seek additional care in the form of physiotherapy, medication, emergency department attendance, specialist consultation or spinal surgery. This model aims to maintain functional levels and reduce care-seeking empowering patients to self-manage their low back pain by offering them a contemporary patient-centred physical activity program with the support of mobile health technology. The outcomes of this trial will have immediate implications for clinical practice.

**Trial registration:**

ACTRN12615000189527 (26-02-2015).

## Background

It is well recognised that low back pain (LBP) is a significant public health problem [1]. Relapses in pain (60 %) and work absences (33 %) are common, making LBP one of the most costly conditions in industrialised societies [2]. The total cost associated with the management of chronic LBP in Australia is estimated at AU$9.17 billion, with the cost of indirect care and productivity losses contributing Ai1U$8.15 billion of this total figure [2]. Cost is expected to grow with the increasing obesity crisis and ageing population worldwide [3].

The clinical course of LBP is intricate. Over a 1-year after discharge from treatment, most patients will still have pain for a sustained period, and a small proportion will still have persistent severe pain [4, 5]. Although randomised controlled trials (RCT) investigating the efficacy of conservative interventions for chronic LBP have found improvements in pain and disability, patients usually exhibit a rapid decline in clinical outcomes, 3 months after treatment discharge [6, 7]. These patients are likely to have a new episode of LBP or continual pain and therefore seek additional health care [8].

Previous research has shown that patients with chronic LBP who engage in moderate to high levels of physical activity have better prognosis in terms of pain, disability, and quality of life than those who fail to maintain adequate levels of physical activity [9, 10]. However, ongoing adherence to such lifestyle behavior is difficult to achieve. Use of communication technologies to increase physical activity has become increasingly popular in recent years, likely because they facilitate access and adherence to health interventions [11]. The use of physical activity monitors is particularly effective in increasing engagement in physical activity [12]. New generations of activity monitors are affordable and provide feedback on daily steps taken and distance travelled using internet, tablet or Smartphone interfaces and social media. A recent systematic review provided strong evidence for the effectiveness of activity monitors such as pedometers to increase physical activity levels for patients with musculoskeletal disorders [13]. Additionally, physical activity monitors have been shown to not only improve physical activity levels, but also to increase function and reduce pain in patients with chronic LBP [14].

Another intervention that may be effective in improving adherence to exercise is health coaching. There is evidence that telephone-based health coaching interventions lead to positive changes in health behaviours. These include increased physical activity participation [14], improved nutrition [15], smoking cessation [16], and better management of chronic musculoskeletal conditions such as osteoarthritis [17]. Coaching interventions have a strong, evidence-based foundation in behaviour-change theories such as Social Influence Theory, Social Cognitive Theory, and the Transtheoretical Model [18] and can be effectively delivered by telephone [19]. There is evidence that health coaching via telephone has the potential to increase activity levels in patients with LBP when compared to usual physiotherapy care alone [20].

However, to the best of our knowledge, there are no studies of a post-treatment physical activity intervention consisting of mobile health and health coaching on long-term outcomes in patients with chronic LBP. Therefore, the primary aim of this RCT is to investigate the effec of a patient-centred physical activity intervention supported by health coaching and mHealth technology, including a mobile web app, tailored physical activity plan, goal setting, and feedback from affordable physical activity monitoring device (*FitBit*) in care-seeking, pain and disability in people with chronic LBP. Secondary outcomes will be physical activity participation and goal attainment. We hypothesise that the use of a patient-centred physical activity intervention will prevent clinical decline in patients who have received the benefits of conservative treatment for chronic LBP, empowering them to self-manage their LBP as well as to prevent worsening of LBP and reduce care seeking.

## Methods

### Study design

We will conduct a single-blinded pilot RCT to evaluate a patient-centered physical activity intervention involving health coaching, compared to standard care (Fig. 1). This trial has been designed according to the CONsolidated Standards Of Reporting Trials (CONSORT) statement [21] and is reported according to the Standard Protocol Items: Recommendations for Interventional Trials (SPIRIT) statement [22].

**Fig. 1 Fig1:**
[figure not shown]
Flow diagram of the study

### Participants

We will recruit 68 patients with chronic LBP from an outpatient physiotherapy department in a public hospital in Sydney, Australia. Consenting participants will be randomly allocated to either the physical activity intervention group (*n* = 34) and receive a patient-centred physical activity promotion program involving health coaching, mHealth tools and advice booklet, or to a standard care group (*n* = 34) who will receive an advice booklet only.

#### Inclusion criteria

Adults over 18 years of age with chronic LBP persisting for over 12 weeks but without radicular symptoms; who have been discharged from a hospital-based, LBP physiotherapy program but still have consistent pain (at least 3 in the Numerical Rating Scale); with regular (weekly) use of a computer or internet-connected mobile/tablet device; and fluency in English (verbal and written).

#### Exclusion criteria

Any spinal surgery in the past 12 months; evidence of nerve root, spinal cord or caudal equine compression; severe spinal stenosis indicated by signs of neurogenic claudication (grade 3 to 4); fibromyalgia, or systemic/inflammatory disorder; comorbid health conditions that would prevent active participation in increasing physical activity levels: cardio-respiratory illnesses; LBP caused by involvement in a road traffic accident in the last 12 months or ongoing litigation; current or planned pregnancy.

### Recruitment method

Treating physiotherapists will screen (all) potential participants from the outpatient Physiotherapy Department of the Liverpool Hospital, South Western Sydney Local Health District, Australia, and inform them about the study. Potential participants interested in participating in the study will receive the Participant Information Statement and be referred to the research team. Patients with chronic LBP who have received any conservative physiotherapy treatment (e.g. exercises, spinal manipulative therapy) and meet the inclusion criteria will be invited to participate in the trial after treatment discharge. At treatment discharge, a research assistant will discuss the study and offer participation to those who meet the inclusion criteria. If they agree to participate a signed consent form will be recorded and baseline data will be collected.

### Group allocation

Random allocation to physical activity or standard care groups will occur after confirmation of eligibility and baseline assessment. Allocation will be blinded and performed using a computer-generated random allocation schedule operated by a remote researcher. The allocation of participants will be concealed by using sequentially numbered, sealed and opaque envelopes.

### Procedures

Patients attending outpatient physiotherapy will be screened by their treating physiotherapists, who will determine eligibility, inform about the trial objectives and invite participation. The ones that manifest interest will be given the Participant Information Statement by their treating physiotherapist and decide if they want to participate in the study. A senior physiotherapist from Liverpool Hospital will be responsible for booking potential participants on their second to last appointment to meet the investigator after discharge. At discharge, patients that agree to participate will be asked to sign the consent form. The assessor will collect demographic and anthropometric data (age, height, weight, waist circumference) as well as baseline data related to the study outcomes. A device able to accurately estimate how physically active a person is throughout the day (*Actigraph*) by measuring 3-dimensional body accelerations will be given to all participants at baseline with clear instructions for use and telephone support available. The *Actigraph* will collect accelerometer-based data over a 1-week period to account for day-to-day variation in physical activity levels [23]. Participants will be provided with pre-paid envelopes to return the devices to the research centres. The *Actigraph* has been successfully used to measure physical activity in large-scale population-based studies internationally [23, 24]. The analyses will be adjusted for accelerometer wear time defined by ‘off time’. Any period of greater than 60 min with no activity at all will be considered to be ‘off time’ and excluded from the analyses. Data will be extracted by a research assistant who will remain blinded to group assignment throughout the trial.

### Interventions

*The physical activity intervention group* will receive a booklet developed by Australia’s Department of Health called ‘*Make your move – Sit less, be active for life!’* The booklet includes information about physical activity and sedentary behaviour. Participants will also be advised to continue their usual activities. The physical activity intervention group will also receive an individualised patient-centred physical activity plan developed with the advice of a health coach. The focus of the patient-centred physical activity will be on a gradual increase in physical activity where participants will be encouraged to devise fortnightly goals to suit and advance their physical activity levels. This intervention will be supported by the use of mHealth, which will include a specifically designed mobile web application (web app) and a physical activity monitoring device (FitBit).

The intervention will address the following factors:

*Health coaching*: This will involve an initial individual face-to-face coaching session. The session can take up to 2 hours and it will be held at the participants’ home. The health coach will be an experienced physiotherapist with a health coaching certification. Their aim will be to motivate and support the participants to increase their physical activity levels. The health coaching session will encompass:Increasing physical activity: Participants will be assisted to develop a physical activity plan that suits their lifestyle preferences. The World Health Organisation (WHO) guidelines addressing healthy adults recommend at least 150 min of moderate-intensity or 75 min of vigorous-intensity aerobic physical activity throughout the week or an equivalent combination of moderate- and vigorous-intensity activity. These recommendations relate not only to sports, but also to other leisure activities, work and transport activity [25]. Suitable local exercise opportunities will be identified using the NSW Ministry of Health’s *Active and Healthy* [26] online database.Decreasing sedentary behaviour: Participants will be encouraged to increase incidental physical activity throughout the day. Options may include travelling by public transportation to work, walking to shops, carrying out a home exercise program, standing at work and spending less time sitting while at home.Goal-Setting: Goals are more effective when they are important to the individual (e.g., self-set rather than assigned), realistic, can be monitored, and when the participant receives positive encouragement [27]. The health coach will jointly work with each participant to set short-term physical activity goals to be achieved fortnightly. The participants’ individual goals will be set taking into consideration the nature of LBP and its normal clinical course. Although the focus of the interaction between the coach and participants is not on symptom monitoring, if significant clinical decline (e.g. participants’ reports of nerve root compromise) is observed, coaches will advise participants to seek appropriate treatment. The health coach will aim to monitor their goals, giving them support and motivation.

This health coaching service will be modelled after the successful [19] NSW Ministry of Health initiative *Get Healthy* service. After the first individual face-to-face coaching session, the health coach will contact each participant fortnightly (12 phone calls over a 6 month period each participant) to assess progress, update the participants’ short-term goals and assist in overcoming barriers – e.g. how to get back to exercise after illness, and provide problem-solving strategies for maintaining physical activity.

*The Fitbit activity monitor and feedback device:* The activity monitoring device will be provided to the participant by the health coach during the initial visit who will also demonstrate its use. Each participant will receive a brief orientation covering this instrument’s proper functions. Telephone support will be offered to participants who have difficulty with the device setup. The *Fitbit* is a personal accelerometer device designed to track physical activity and sleep. This device logs individual data on physical activity and provides feedback on the number of steps taken in each 24-hour period; the distance walked daily; calories burned; and sleep duration and quality. The number of steps taken per day, week, and month are also summarised graphically on the device’s website (http://www.fitbit.com/au) or a Smartphone application, which will also be demonstrated to the participant.

*The IMPACT web app:* The IMPACT web app: A mobile web app will be built and hosted by the University of Sydney. The app will be customised specifically for the purposes of this project to allow participants to monitor their goals and their physical activities. Participants will be able to access the app at any time and write reports about their physical activity related goals to their health coach as well as receive coach-tailored feedback. In addition, each participant will receive a quick questionnaire every week to monitor their pain levels, based on the Numerical Rating Scale; disability, based on the Rolland-Morris disability questionnaire and care-seeking associated with LBP. This questionnaire was created specifically to this project. The health coach will have the ability to view the participant’s report and communicate with them by phone fortnightly to discuss their goals and update them according to their reports and feedback. Personalised messages constructed by the health coach will be sent every week to encourage participants to achieve their goals. In summary, the IMPACT web app will be designed to facilitate monitoring achievement and providing updates on participants’ goals, encouraging them to engage in physical activity and track potential adverse events.

*The standard care control group* will receive the ‘*Make your move – Sit less, be active for life!’* booklet and will be advised to work towards increasing their physical activity levels and achieving their two long-term goals as defined at baseline.

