### Outcomes

Primary outcomes will be collected at baseline and weekly over a period of 6 months of intervention through an online, self-reported electronic questionnaire, created by the research team. The physical activity intervention group will receive a reminder every week through the web app with a brief questionnaire related to the primary outcomes. The standard care group will receive a SMS reminder every week with a link to the same questionnaire. Secondary outcomes will also be collected electronically at baseline, 6 and 12 months. Both groups will fill out the same questionnaire through the same system. The electronic version of the baseline questionnaires and the weekly questionnaire were created by the research group and will be hosted by the University of Sydney.

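### Adverse-event tracking is described only as a function of the intervention arm's web app, so events outside the shared weekly questionnaire would be ascertained unequally

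*Protocol article*

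**What the plan says.** In the protocol article, the Interventions section ends its description of the IMPACT web app with a summary of what the app is for: monitoring and updating goals, "encouraging them to engage in physical activity and track potential adverse events". This is the only place where the article mentions adverse events.

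The same section makes the app, together with the activity monitor, a component of the intervention. For the other arm, the Abstract (Methods/Design) says: "The standard care group will receive the physical activity advice booklet only". The Interventions section adds that controls are also advised to become more active.

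The Outcomes section describes weekly data collection in both arms. For the intervention arm: "The physical activity intervention group will receive a reminder every week through the web app with a brief questionnaire related to the primary outcomes". For controls: "The standard care group will receive a SMS reminder every week with a link to the same questionnaire". It then states: "Both groups will fill out the same questionnaire through the same system". The web app paragraph and the Primary outcomes section give the content of this form as a pain rating, Roland-Morris disability, and care-seeking associated with low back pain (practitioner visits, self-management and medication).

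The intervention arm also has regular contact with a health coach. If significant clinical decline "is observed, coaches will advise participants to seek appropriate treatment".

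**The concern.** Harms can be compared between arms only if they are looked for in the same way in both. Here the one described tool for tracking adverse events belongs to one arm. Controls are also encouraged to raise their activity, so they too may fall, strain a joint or have another event unrelated to the back, but no described item asks them about it.

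If the text is followed as it stands, a higher count of such events in the intervention arm could reflect closer observation and not more harm. The Sample size calculation section says that this pilot is to inform the feasibility and design of a larger multi-centre trial, so a distorted safety picture could be carried into that trial.

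**Working it through.** The point rests on the text and not on a stated figure, so the first step is to set out, for each kind of event, which described route exists in each arm.

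| Kind of event | Intervention arm | Standard care arm |
|---|---|---|
| Worse back pain | Weekly form | Same weekly form |
| Worse back-related disability | Weekly form | Same weekly form |
| Care-seeking for low back pain | Weekly form | Same weekly form |
| Other events (for example a fall or a non-back injury) | Web app, by its stated tracking function | None described |

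Rows one to three follow from the Outcomes and Primary outcomes sections and show no difference between arms. Row four follows from the web app paragraph in Interventions, read with the Abstract's account of what controls receive. The asymmetry is confined to that row.

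The weekly form does not clearly fill the row. The Outcomes section calls it "a brief questionnaire related to the primary outcomes", and each listed item concerns pain, back-related disability or care-seeking for back pain.

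The second step is to see how unequal capture acts on a comparison. Let p be the true risk of a row-four event, equal in both arms; let a be the proportion of such events captured in the intervention arm and c the proportion captured among controls. Then

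observed risk difference = p·a − p·c = p(a − c).

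The document gives none of p, a or c. Taking a = 1 throughout, and assumed values for the others:

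- p = 10%: c = 1 gives 10 × (1 − 1) = 0 points; c = 0.5 gives 10 × (1 − 0.5) = 5 points; c = 0 gives 10 points.
- p = 20%: c = 1 gives 0 points; c = 0.5 gives 20 × (1 − 0.5) = 10 points; c = 0 gives 20 points.

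These values show direction and mechanism; they are not estimates for this trial. The bias vanishes when capture is equal (a = c), which is what a common item put to both arms at the same frequency aims to secure.

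**The case against.** The strongest reply is that the sentence about adverse events opens as a summary of the app features just listed, and the only structured health item among those is the weekly questionnaire, which controls also complete. On that reading, tracking runs through a shared instrument and there is little asymmetry. The reading is possible, and the article does not settle it. But it does not fully answer the point: the items listed for that questionnaire concern pain, disability and back-related care-seeking, so a fall or a knee injury would still have no described place in it.

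A second reply is that this is a condensed article, and that adverse-event definitions, forms and reporting procedures may stand in a full protocol that is not shown. That is right, and their absence is not the complaint. The point concerns what the article does state: it places tracking in a tool given to one arm.

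A third reply is that no between-arm safety comparison is planned. Adverse events appear neither among the outcomes nor under Statistical analysis. This also stands, and it makes the consequence conditional: the bias bites if events are compared or reported by arm.

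A reader might infer more than the text supports, in three ways:

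- *That harms cannot be compared at all, or that controls have no means of reporting anything.* They report pain, disability and back-related care-seeking every week on the same form and system as the intervention arm.
- *That the weekly prompts are extra adverse-event contacts in one arm.* Both arms are prompted weekly to the same questionnaire.
- *That the coach calls are formal adverse-event capture.* The Health coaching text says that symptom monitoring is not their focus, and it describes advice to seek treatment, not the recording of events. At most, coach contact could bring events to light informally.

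**Conclusion.** The concern holds in a limited form. As written, ascertainment is equal for back-related worsening and care-seeking. It is unequal for other activity-related events, which have a described tracking route only in the intervention arm. Any comparison of those events between arms would be open to detection bias, tending to make the intervention look less safe than it is.

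The size cannot be derived from the document. It depends on the true event risk and on how completely control events come to light, neither of which is given.

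The conclusion assumes that the weekly questionnaire contains no adverse-event item beyond the content described. If it does contain one, put identically to both arms, the point reduces to a missing sentence. This is a correction worth making because it costs little; it does not undermine the trial's primary comparisons.

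**What to change.** 1. Add the same brief adverse-event items (for example new injury, fall, hospital visit) to the weekly questionnaire that both arms already complete, with the same wording and frequency.
2. State that any between-arm statement on safety will rest on those items only.
3. Report events found through app-only features or coach contact separately, labelled as intervention-arm only.
4. If the form already includes such an item, say so in the Outcomes section and reword the web app paragraph so that tracking is not presented as a function of the app alone.

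The cost is one to three extra questions in an existing electronic form, a small weekly burden on participants, and no new visits or systems.
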